**Fig. 1 Fig1:**
[figure not shown]
Synopsis of the study

In the control group, patient management will be based on clinical examination. Gastrografin will not be used in the control arm, as data from a recent randomized clinical trial that included 242 patients (ABOD study [10]), combined with the results of a meta-analysis performed in 2015 that included 990 patients, failed to demonstrate the value of gastrografin to reduce the surgery rate and length of stay. Gastrografin may therefore no longer be indicated in this setting. The use of gastrografin could also introduce a bias in the interpretation of the outcome, as the outcomes could be considered to be related to gastrografin and not exclusively to the algorithm. Conservative management will be continued for 48 h in the absence of signs of bowel ischemia and the presence of bowel function.

From 48 h after the initiation of conservative management or in absence of bowel function, operative management (adhesiolysis or bowel resection) will be performed.

There is no blinding procedure, as blinding is not possible/necessary because each center will be randomized to one study arm and all patients in each center will be managed according to the same strategy.

### Outcomes

The primary endpoint will be the proportion of patients achieving the textbook outcome, defined as patients either appropriately undergoing surgery (ischemia confirmed at operation ± resection) or appropriately managed conservatively (no need for surgery) with no major postoperative complications (Clavien–Dindo ≥ 3) and a medical length of stay < 5 days (defined as the time at which the patient is medically eligible for discharge), with no postoperative consultation, rehospitalization, or reoperation within 90 days after randomization. The textbook outcome is defined as that proposed by Kolfschoten [14] for colon cancer resection. The primary endpoint will be analyzed by an open-label design. The centers will record all cases of (i) no readmission, (ii) no unplanned consultation for nausea, vomiting, and/or the absence of gas and/or stool, (iii) no hospitalization, (iv) no reoperation, and (v) no recurrence that could occur after the patient’s discharge and before the two visits scheduled in the protocol (1 and 3 months). If the quality of the completion of the primary endpoint is not sufficient after monitoring of the first-recruited patients, the adjudication committee will be contacted.

The secondary endpoints are the 1-, 3-, 6-, 9-, 12-month recurrence rates, defined as a new episode of adhesion-related small bowel obstruction, the EVAN G score to evaluate patient satisfaction at postoperative month 1 [15], the Clavien and CCI scores to assess morbidity evaluated after the patient’s discharge at postoperative month 1, the hospital length of stay, defined as the interval between admission to the emergency department and discharge from the ward, and the cumulative length of stay, defined as the total number of days of hospitalization related to ASBO at postoperative month 12.

### Sample size

According to Williams, Ellozy, Fraser et al., 60% of patients were successfully managed without the algorithm. Ryan also reported that 62% of patients were not readmitted or hospitalized for ASBO at postoperative day 90. With our local data showing successful management with the algorithm in 78% of patients and assuming a 62% success rate without the algorithm, with a two-sided alpha risk of 5%, a power of 80%, an intra-class correlation coefficient of 0.015, 16 anticipated clusters (centers), a coefficient of variation of 0.15 for cluster size, 372 patients would need to be recruited. By assuming 5% of patients lost to follow-up, 414 patients need to be enrolled.

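### The enrolment target of 414 does not follow from 372 patients and 5% loss, which give 392; 414 is what a 10% allowance gives

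*Protocol article*

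**What the plan says.** The Sample size section of the protocol article works in two steps.

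1. **Base number.** It takes 78% success with the algorithm, from the investigators' own data, and 62% without it. The error rates are a two-sided 5% alpha and 80% power. The clustering inputs are "an intra-class correlation coefficient of 0.015", 16 centres, and "a coefficient of variation of 0.15 for cluster size, 372 patients would need to be recruited".
2. **Loss to follow-up.** The next sentence reads: "By assuming 5% of patients lost to follow-up, 414 patients need to be enrolled".

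The 5% is the only step described between 372 and 414. The ICC, the number of centres and the variation in cluster size have already gone into the 372. Empty clusters are handled in the design section by a commitment from each principal investigator before randomization, not by extra patients. The article gives no second loss rate, no non-evaluable fraction and no rounding rule.

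**The concern.** A 5% allowance should raise a sample size by a little over 5%. Going from 372 to 414 raises it by 11.3% (42/372), too much for rounding to explain.

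These figures set the recruitment target and the attrition that the 90-day primary endpoint is planned to absorb. The direction of the correction matters:

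- If 5% is right and 372 is the need, the plan enrols 22 patients more than its own calculation supports.
- If 10% was intended, someone who trusts the 5% and cuts the target to 392 would be left with 392 × 0.90 = 352.8, about 353 patients. That is 19 short of the stated 372.

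**Working it through.** **Inputs, all from the Sample size section:** base 372; loss 5%; target 414; success 62% and 78%; two-sided alpha 5%; power 80%; ICC 0.015; 16 centres (8 per arm at 1:1); coefficient of variation (CV) of cluster size 0.15.

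**Step 1: try to reproduce 414 from 372 and 5%.**

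| Method | Calculation | Result |
|---|---|---|
| Divide by retention | 372/0.95 = 391.6 | 392 (196 per arm) |
| Multiply by 1 + loss | 372 × 1.05 = 390.6 | 391 |
| Divide, then round up per centre | 391.6/16 = 24.5, so 25 × 16 | 400 |
| Round up per centre before and after | 372/16 up to 24; 24/0.95 up to 26; 26 × 16 | 416 |

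None gives 414. The last comes close, but it rounds twice, and 414 is not a multiple of 16.

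**Step 2: find the loss rate that 414 implies.**

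- Implied allowance: 1 − 372/414 = 42/414 = 10.1%.
- At 10%: 372/0.90 = 413.3, rounded up to 414 (207 per arm). This matches exactly.

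**Step 3: work back from 414 at 5%.** 414 × 0.95 = 393.3, so about 393 patients would remain, 21 more than the stated need.

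**Step 4: check whether 372 is plausible.** With n the per-arm size under individual randomization and 8 centres per arm, the clustered size per arm is

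n(1 − ICC) / [1 − n × ICC × (1 + CV²)/8].

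| Formula for n | n per arm | Clustered total |
|---|---|---|
| Normal, unpooled variance | 124.8 | 323 |
| Normal, pooled variance | 128 | 334 |
| Normal, pooled, continuity-corrected | 140 | 377 |
| t distribution with 14 df, unpooled | 144.4 | 393 |

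For the continuity-corrected row: 140 × 0.985 = 137.9; 140 × 0.015 × 1.0225/8 = 0.268; 137.9/0.732 = 188.5 per arm, 377 in total. That is within 3% of 372. The uncorrected normal formulas fall 10% to 13% below 372.

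The t-based row deserves notice. It gives 393, and 393/0.95 = 413.7, which rounds up to 414. So 414 with 5% loss would be consistent if the base had been about 393. The article does not name its formula, so this check cannot settle which figure is the slip.

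**The case against.** The strongest counter-argument is about consequence. If 372 and 5% are taken at face value, enrolling 414 leaves more patients than needed. Power is not harmed, and no estimand, analysis or patient decision changes. This stands: it is an error in the sample-size statement, not a threat to validity.

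A second objection is that 10% is an inference. Applying 5% twice and rounding per arm also reaches 414: 186/0.9025 = 206.1, so 207 per arm. On the total it gives 372/0.9025 = 412.2, so 413. This also stands, in that 10% is the simplest explanation but not a confirmed one. It does not rescue the text, which describes a single 5% loss.

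A third objection is that 372 is reproduced only with a continuity correction the article does not mention, so the base should not be declared sound. That is fair, and the t-based result makes a base of about 393 a real possibility. It widens the choice of which figure to correct but does not make 372, 5% and 414 agree.

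Condensation for a journal is no defence. All three figures are printed, and no further detail in a fuller document would make one 5% allowance turn 372 into 414.

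**Conclusion.** The concern holds. From 372 patients, a 5% loss gives 392, not 414. The discrepancy is 22 patients (22/392 = 5.6%), and the allowance implied by the printed figures is 10.1% rather than 5%.

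This rests only on the three figures in the Sample size section and on the usual inflation by one minus the loss rate. Multiplying by 1.05 instead changes the answer by one patient. Which figure is wrong cannot be established from the article. A 10% allowance is the most direct explanation, and a base of about 393 is the main alternative. The practical effect is modest while 414 is kept. It would become material if the target were cut to 392 and losses ran at 10%.

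**What to change.** The sponsor should check the original calculation and print one consistent set:

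- **Keep 414 and state 10% loss to follow-up**, if that was the planning assumption; or
- **keep 5% and state 392**, if 5% was the assumption and 372 is the need; or
- **keep 414 and 5% and replace 372 with about 393**, if the original output shows that base.

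Naming the sample-size formula, including any continuity correction or t-based adjustment for 16 centres, would let a reader confirm the choice. The corrected set should be carried to any other trial document that repeats these figures; in the article they appear only in this section.

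The cost is one sentence. The first and third options leave recruitment as it is. The second lowers the target by 22. None needs extra patients.

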### Study calendar

The planned duration of inclusion is 24 months and the duration of participation for each participant is three months. The planned total duration of the study is 27 months. This is the version 1 of the protocol (17/11/2021).

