## Methods/design

### The aim, design, and setting of the study

#### The aim

The primary objective of the study is to assess the impact of a PCT-based algorithm on the textbook outcome at postoperative day 90. The secondary objectives are to compare short-term and long-term recurrence rates, quantify and compare patient satisfaction, compare morbidity according to the type of management, compare the length of stay, propose other markers of ischemia (copeptin, proadrenomedullin) to reinforce the value of PCT in the early stages of ASBO, and perform a cost-effectiveness analysis.

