## Abbreviations

PCT: Procalcitonin
ASBO: Acute adhesion-related small bowel obstruction
CT scan: Computed tomography scan
EVAN G: Evaluation du vécu de l’anesthésie générale, means Evalaution of the satisfaction of the perioperative period
CCI: Charlson Comorbidity Index

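### Participation is fixed at three months per patient, yet four secondary endpoint measures and one objective need follow-up to months 6, 9 and 12

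*Protocol article*

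**What the plan says.** Three places in the protocol article bear on this.

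- **Study calendar.** "The planned duration of inclusion is 24 months", and then "the duration of participation for each participant is three months. The planned total duration of the study is 27 months".
- **Outcomes.** The text on recording primary-endpoint events refers to two scheduled visits, at 1 and 3 months. The next paragraph reads "The secondary endpoints are the 1-, 3-, 6-, 9-, 12-month recurrence rates" and adds a cumulative length of stay, defined as "the total number of days of hospitalization related to ASBO at postoperative month 12".
- **The aim.** The secondary objectives are to "compare short-term and long-term recurrence rates, quantify and compare patient satisfaction", among others.

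The article describes no visit, contact, record linkage or extended follow-up after month 3.

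On a smaller matter, Outcomes uses the Clavien and CCI scores to assess morbidity at month 1, while the Abbreviations list gives "CCI: Charlson Comorbidity Index".

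**The concern.** The calendar and the endpoint list cannot both be followed. A patient whose participation ends at three months is out of the study before months 6, 9 and 12, so the endpoints at those times have no planned source of data. This is a conflict between two explicit statements, not a detail left out.

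At stake are the long-term part of the recurrence objective, three of the five recurrence time points, and the month-12 cumulative stay. If the conflict is noticed only after patients have completed three months, prospective data from those patients will be harder to recover. If some centers go on collecting data and others stop, completeness could differ by center. In a cluster-randomized trial with 16 centers, that can mean it differs by arm.

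**Working it through.** **Inputs, all from the protocol article**

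- Inclusion period: 24 months (Study calendar)
- Participation per patient: 3 months (Study calendar)
- Total duration: 27 months (Study calendar)
- Scheduled visits named: months 1 and 3 (Outcomes)
- Recurrence time points: months 1, 3, 6, 9 and 12 (Outcomes)
- Cumulative stay: month 12 (Outcomes)
- Planned enrolment: 414 (Sample size), used only to turn shares into patient counts

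**Step 1: reproduce the stated total.** Total duration = inclusion period + follow-up of the last patient = 24 + 3 = 27 months. This matches exactly, so the three-month participation is part of the calendar and not an isolated slip.

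**Step 2: compare each late time point with the per-patient limit.** Month 6 exceeds it by 6 − 3 = 3 months, month 9 by 9 − 3 = 6 months, and month 12 by 12 − 3 = 9 months. Under the stated limit, 0% of participants are under follow-up at these times. Months 1 and 3 lie within it.

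**Step 3: duration needed if everyone is followed to month t.** Total = 24 + t.

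**Step 4: what the 27-month total alone would allow.** Suppose the per-patient limit is ignored and accrual is uniform over 24 months (my assumption). A patient reaches month t by calendar month 27 only if included by month 27 − t, so the share is (27 − t)/24.

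| Time t | Total needed (24 + t) | Share reaching t by month 27 | Of 414 | Share not reaching t |
|---|---|---|---|---|
| 6 months | 30 | 21/24 = 87.5% | about 362 | 12.5% |
| 9 months | 33 | 18/24 = 75% | about 310 | 25% |
| 12 months | 36 | 15/24 = 62.5% | about 259 | 37.5% |

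Patients missing at month 12 would be those included after month 15. Following everyone to month 12 takes 36 months, which is 36 − 27 = 9 more than stated.

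Times are counted from inclusion. The cumulative stay is labelled postoperative; for an operated patient that clock starts no earlier than inclusion, so the gap would not shrink.

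**The case against.** Several points can fairly be made on the other side.

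- **Only secondary endpoints are involved.** This is correct. The 90-day primary endpoint, the sample size and the 1- and 3-month recurrence rates stand as they are.
- **The article is condensed, and the full protocol may describe later follow-up.** That would excuse silence, but the article is not silent: it states a three-month limit and month-12 endpoints. An analysis plan cannot lengthen participation.
- **The two visits are named only in connection with the primary endpoint.** This is fair, since that phrase is not a full visit schedule. The calendar sentence carries the point, and the visits merely agree with it.
- **Early recruits reach month 12 within 27 months.** Under uniform accrual about 62.5% would, but only if the per-patient limit is disregarded.

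A reader might also be tempted by stronger readings, which the document does not support.

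- *The late endpoints are impossible to obtain.* Later collection from hospital records is conceivable. What can be said is that the stated participation and visits do not provide for it.
- *The cost-effectiveness analysis fails.* The article gives neither its time horizon nor its inputs, so no such link can be shown.
- *The satisfaction endpoint applies only to operated patients.* The endpoint is "the EVAN G score to evaluate patient satisfaction at postoperative month 1", and the abbreviation list glosses the score as "Evalaution of the satisfaction of the perioperative period". The name and gloss raise a question about conservatively managed patients, but the instrument itself is not shown and nothing restricts who completes it. The article also uses the word postoperative for the whole study population. The share of patients who will be operated on here is unknown, and operative rates quoted from other studies cannot stand in for it.

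**Conclusion.** The contradiction is real and can be confirmed from the document's own figures. Followed as written, the calendar leaves four secondary measures without planned data for any participant: recurrence at 6, 9 and 12 months, and cumulative stay at month 12. The long-term recurrence objective then has nothing behind it beyond month 3. The statement that no participant is covered rests on the per-patient limit alone. The 27-month total alone would leave about 37.5% short of month 12, assuming uniform accrual.

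The statements must be reconciled, ideally before patients complete three months. The effect is confined to secondary endpoints.

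The CCI entry is a separate and minor matter, probably a wrong line in the abbreviation list. A comorbidity index describes underlying illness and does not measure morbidity after management. Clavien grading is listed alongside it, so the morbidity objective is not lost.

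**What to change.** Bring The aim, Outcomes and Study calendar into agreement by choosing one of two options.

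**(a) Keep the late endpoints.** Set participation to 12 months and total duration to 24 + 12 = 36 months. Take recurrence and ASBO-related stays after month 3 from hospital records or a telephone contact, by the same procedure in every center, and cover this in the consent. The cost is an amendment, with a new information sheet and consent form where the constraints on patients change (Protocol amendment section), and 9 more months of study.

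**(b) Keep three months and 27 months.** Remove the 6-, 9- and 12-month recurrence endpoints and the long-term part of the recurrence objective, and end cumulative stay at month 3. The cost is that long-term recurrence is no longer answered. This removes an objective and several endpoints, so the sponsor should check whether it counts as a substantial modification under the Protocol amendment section.

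**Minor.** Correct the expansion of CCI so that it names a measure of morbidity after management, or report Clavien grades alone. This is a one-line change.

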### Randomization procedure

After obtaining consent from potential participants, randomization will be performed using computer-generated random numbers by the trial methodologist before patient recruitment. Each of the sixteen centers will be assigned to one arm (with or without the PCT algorithm) in order to avoid contamination between the two arms. In the case of typing errors or missing data, a message will indicate the corrections to be made to allow randomization of the patient.

### Stopping rules

The patients can withdraw their consent and leave the study at any time, for any reason. In case of anticipated stop, the investigator must precise the reason as complete as possible. The investigator can terminate the patient’s participation for any reason in the patient’s best interests, especially in the presence of adverse events. The study can be stopped in the case of unexpected serious adverse events.

In the event of premature discontinuation of the study, exclusion from the study, study drop-out or major protocol deviation, patients will be followed as usual.

### Ethics

The study received an agreement from the Comité de protection des personnes under the number 2017-A00613-50/SI: 18.09.12.65718 on the 29th of November 2018.

### Access to data

The sponsor is responsible for obtaining the agreement of all parties involved in the study to ensure direct access to all study sites, source data, source documents, and reports to enable the sponsor to control data quality and perform an audit. Investigators will provide access to documents and individual data strictly required for monitoring, quality control and audit of the biomedical study to authorized persons, in accordance with current statutory and regulatory provisions (Articles L.1121-3 and R.5121-13 of the French Public Health Code). Any original document or object establishing the existence or accuracy of a data point or information recorded during the study is defined as a source document (medical file, original copy of clinical, laboratory test and imaging results, examination reports, etc.). In accordance with current statutory provisions (Articles L.1121-3 and R.5121-13 of the French Public Health Code), persons with direct access to source data will take every necessary precaution to ensure the confidentiality of information relating to investigational medicinal products, studies, participants, especially concerning the identity of these subjects, as well as the results obtained. These persons, like the investigators themselves, are bound by professional secrecy. All data concerning participants collected during or at the end of the study will be coded by the investigators (or any other specialists involved) before being sent to the sponsor. The name and address of study participants will never be directly visible. Only personnel participating in the study will have access to the patients’ data.

Confidentiality of data will be ensured by coding patient information based on the following data:Their initials: the first letter of the last name and the first letter of the first name,A 5-digit study number: a 2-digit number corresponding to the study center number, followed by a 3-digit number from 001 to 999 attributed by order of inclusion in the study.

The sponsor will ensure that each study participant has given his/her written consent for access to his/her personal data as strictly required for quality control of the study.

### Protocol amendment

Any substantial modification, i.e. any modification likely to have a significant impact on the safety of study participants, the conditions of validity and results of the study, the quality and safety of investigational products, the interpretation of scientific documents that support the study or the study procedures, must be described in a written amendment that will be submitted to the sponsor, and must be approved by the ethics committee (CPP) and authorized by ANSM before implementation.

Non-substantial modifications, i.e. those with no significant impact on any aspect of the study, will be notified to the CPP for information purposes.

All amendments must be validated by the sponsor, and by all parties involved in the study concerned by the modification, before submission to the CPP and ANSM. This validation may require a meeting of the scientific committee and/or independent monitoring committee.

All investigators participating in the study must be informed about all protocol amendments. The investigators must undertake to comply with the contents of all protocol amendments.

Any amendment that modifies patient care or the benefits, risks and constraints of the study will require a new patient information sheet and a new informed consent form, according to the aforementioned procedure.

